### Randomisation

The randomisation is carried out as a cluster randomisation allocating the nursing homes either to the intervention or to the control group. Randomisation is performed by an experienced biometrician at Hannover Medical School after the recruitment of patients (BW). The allocation sequence is computer generated and concealed from researchers and interviewers. The randomisation is stratified by centres to ensure a balance in the number of nursing homes and patients allocated to each treatment group within the centres.

### Blinding

Due to the complex nature of the intervention, blinding of participants, health care providers and data collectors is not possible. The randomisation is performed after the recruitment of nursing homes, pharmacists, GPs and nursing home residents.

### Data collection methods

Resident-related data are collected by the study personnel via standardised questionnaires and additionally according to the NHR’s records. Then the data is entered into an internet based electronic data capture system at two time points: t0 after obtaining written informed consent and randomization and before starting the intervention, t1 after the intervention period (month six).

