## Methods

### Design and setting of the study

The multicentre cluster randomised controlled trial (cRCT) is conducted in four geographical regions in Germany (Hannover, Rostock, Düsseldorf and Tübingen), of which two have a wide rural periphery and two are more urban based. Clustering takes place at the level of nursing homes. Together, the four study centres will include a total of 760 NHR at baseline (Fig. 1).

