### Intervention

Following baseline assessment (t0), the intervention will be conducted and its effects measured at 6 months follow-up (t1) (Fig. 1). The intervention consists of four elements.

Firstly, the community pharmacists in charge of the nursing homes receive a special two-day training (ATHINA = Arzneimitteltherapiesicherheit in Apotheken i.e. medication therapy safety in pharmacies) [25] in performing an IT-based medication review and a further one-day training in geriatric pharmacotherapy especially designed for the study (HIOPP-3 training) based on programmes developed for previous studies (AMTS AMPEL I and II; [2, 22]). After the completion of baseline documentation by study nurses the pharmacists perform a structured medication review. Pharmacists are trained to consider 13 potential medication problems for their medication review:no indication for a certain drug based on available diagnosesnegative benefit-risk profile (according to pharmacist’s judgement)potential relevant drug interactionpotential relevant drug-disease interactionduplicate prescriptionPIM in elderly (PRISCUS list) [26]potentially relevant side effectsapplication/usage inappropriatepossible underdosingpossible overdosingcontraindicationassess duration of treatmentother reasons

The results and advice will be documented in secuTrial® and transferred to a special fax template (“medication check fax”), to be sent to the responsible GPs. The GPs in turn assess the pharmacists’ suggestions and amend their medication prescriptions, if they deem the suggested changes appropriate. Additional prescribing specialist doctors (e.g. psychiatrist) may also be informed of medication changes, either via the GP or the nursing home.

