Secondly, change management principles are introduced to enhance the involved professions’ understanding of roles and interprofessional communication as a vital part of the medication management [27]. Change management support is provided by means of three workshops which are conducted in the nursing home and to which all participating professional groups are invited. The first workshop is held around the time of baseline data collection. Trained study personnel and project managers inform the attendees about the study and its goals. They facilitate a strength and weaknesses analysis of the current medication management structures and processes. Input from all attendees is noted on cue cards. Following a discussion, specific goals for each nursing home are set and suitable tools and processes to facilitate the change process (see below in Table 2) are introduced to support communication and collaboration. Finally, an intervention handbook describing all elements of the intervention/tool box is handed out.

**Table 2 Tab2:** Toolbox content

Name	Function
Thematic map for drug safety (German name: AMTS-AMPEL-Karte)	• clues for drug induced symptoms • uses a simple traffic light system:red: for high risk drugs yellow: weighty symptoms to look out for green: clues for the need of clinical monitoring • to be used by nursing staff and GPs
Additional information for the thematic map for safety in drug therapy	• easy explanations for drugs and symptoms • to be used by nursing staff
Treatment observation sheet (German name: Therapiebeobachtungsbogen)	• to be used by nursing staff • records ongoing/new symptoms in NHR • to look out for adverse drug events
Ward round tool	• to be used in common ward roundsof all 3 partaking professions • for medical and pharmacological issues of NHR
PRISCUS list [26]	• List of potentially inappropriate medications (PIM) for senior citizens • contains 83 PIM
Hospital discharge tool	• communication aid between nursing staff and GPs • used after discharge from hospital

A second change management workshop is held 2 months later. All stakeholders discuss how they have experienced the initiation of change and what further support or agreements are necessary to progress in improving their medication management. New tools can be introduced at this stage. Attendees are also asked to finalize an action plan detailing how they wish to cooperate in the following months and which tools they intend to use.

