### Challenges

We are aware of several challenges pertaining to the conduction of the trial in the fields of recruitment, motivation of the professionals in the intervention and control groups, and drop out.

The recruitment of nursing homes is limited due to the difficulty matching interested nursing homes with responsible pharmacists and interested GPs. Once the matching has taken place, recruiting NHR is confined to only those, whose health professionals have consented. Moreover, often legal caretakers are to be involved who additionally have to consent.

We also expect difficulties in keeping nursing homes, GPs and pharmacists allocated to the control groups motivated to provide current diagnoses and laboratory parameters of their participating patients as they will not receive a compensation for this. Once community pharmacists are randomised into the control group they do not perform a medication review and might feel disappointed. We aim to overcome these obstacles by offering nursing homes, GPs and pharmacists in the control group access to intervention procedures at the end of the study.

Finally, we anticipate an extensive loss-to-follow up of the NHR due to a short life expectancy [30], or discontinuation of participating health professionals. Our sample size calculation addresses this issue allowing a drop out of 20% of NHR within the 6 months intervention phase.

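### Baseline is scheduled after randomisation, collected by unblinded staff and close to the first workshop, so baseline values can depend on the arm and are not safe adjustment covariates

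*Protocol article*

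**What the plan says.** All references are to the protocol article.

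- **Order of recruitment and randomisation (Blinding; Randomisation agrees):** "The randomisation is performed after the recruitment of nursing homes, pharmacists, GPs and nursing home residents".
- **Timing of baseline (Data collection methods):** t0 is taken "t0 after obtaining written informed consent and randomization and before starting the intervention".
- **Start of the intervention (Intervention, opening):** "Following baseline assessment (t0), the intervention will be conducted".
- **First workshop (Intervention, second element):** "The first workshop is held around the time of baseline data collection". At this workshop goals are set for the home, tools are introduced and the handbook is given out.
- **Who collects data (Data collection methods; Blinding):** "Resident-related data are collected by the study personnel via standardised questionnaires", with additional use of residents' records; "blinding of participants, health care providers and data collectors is not possible".
- **Concealment (Randomisation):** the allocation sequence is concealed from researchers and interviewers.
- **Baseline content (Recruitment strategy):** diagnoses, laboratory parameters obtained from GPs, symptoms and prescriptions. The MMSE has its own part of the consent form.
- **Expected difficulty (Challenges):** keeping professionals "allocated to the control groups motivated to provide current diagnoses and laboratory parameters of their participating patients", because they are not paid for it.
- **Analysis (Statistical analyses):** mixed models with nursing home as random effect, adjustment for possible imbalances and confounders, intention-to-treat.

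**The concern.** A baseline measurement is a safe covariate because allocation cannot have affected it. That guarantee is lost once the measurement is taken after allocation by people who may know the arm. Here nothing stated in the article requires the loss, since residents have consented before randomisation and t0 could be taken then.

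Three routes are open:

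1. Interviewers, residents and nursing staff may answer or score differently when they know the arm.
2. Unpaid control-arm professionals may supply diagnoses and laboratory values less completely.
3. The first workshop may come before some t0 data in intervention homes.

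An apparent baseline imbalance could then be an artefact or an early effect, and the plan would adjust for it.

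**Working it through.** The article gives no figure for this point, so the check is mainly a comparison of its sections.

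**Step 1: sequence.** Blinding and Randomisation give: recruit, then randomise. Data collection methods gives: consent, randomise, t0, intervention. Together: recruit, randomise, t0, intervention. So t0 falls after allocation, by the article's own statement.

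**Step 2: where the workshop falls.** The opening of Intervention and Data collection methods put the whole intervention after t0. The description of the second element puts the first workshop around t0. The workshop belongs to the intervention, so these statements do not fix one order. Incentives adds that pharmacists allocated to the intervention arm are trained in a preparatory phase, whose timing relative to t0 is not stated.

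**Step 3: knowledge of arm at t0.** Randomisation conceals the sequence, which protects the assignment of homes. Blinding says data collectors cannot be blinded. Concealment of the sequence does not cover a measurement made after allocation, and the article does not say what interviewers know at t0.

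**Step 4: exposure by type of variable.**

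| Baseline item | Route | Exposure |
|---|---|---|
| MMSE, interview items | unblinded assessor or respondent | highest |
| GP diagnoses, laboratory values | willingness to supply differs by arm | high, mainly through missingness |
| Medication status from records | only a real prescribing change before t0, or selective recording | lower |

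**Step 5: what adjustment would do (illustration on assumed values).** The planned effect is 50% − 30% = 20 points. Let s be the amount by which allocation lowers recorded t0 prevalence in the intervention arm. Let b be the weight that the analysis gives to baseline: 0 with no adjustment, 1 for a change from baseline. On a linear scale, which only approximates the planned logistic model:

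apparent effect = 20 − b × s

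| s (assumed) | b = 0 | b = 0.5 | b = 1 |
|---|---|---|---|
| 2 points | 20 | 19 | 18 |
| 5 points | 20 | 17.5 | 15 |
| 10 points | 20 | 15 | 10 |

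A shift of the opposite sign would overstate the effect by the same amounts. Neither s nor b is in the article. What the table does establish is the b = 0 column: without baseline adjustment, distorted t0 values do not enter the six-month comparison.

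**The case against.** The strongest defence is that the medication review waits for baseline. Recruitment strategy lets pharmacists begin only when the study nurse reports complete data, and Intervention repeats that the review follows baseline documentation. A reader might infer that prescribing in intervention homes was already being changed before t0. The documents do not support this. The route from pharmacist to GP is closed until t0 is complete, and the wording on the workshop does not say that it comes first. What remains is a possibility through the workshop, and perhaps the training, and an order that is not fixed.

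A reader might also infer from "the four study centres will include a total of 760 NHR at baseline" that residents lost between randomisation and t0 are dropped. That does not follow. The abstract says 760 residents will be recruited, recruitment precedes randomisation, and the analysis is by intention-to-treat. No section defines the analysed set as those present at t0. The interval between allocation and t0 is not given either, so losses in it cannot be counted.

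On the GP data, Table 1 makes willingness to supply them an eligibility criterion, and Challenges offers control-arm professionals access to the intervention procedures at the end of the study. Challenges also does not name t0. The link to t0 comes from Recruitment strategy, which lists these items as baseline data. The criterion and the offer reduce the risk, but a difference by arm is still what the authors expect. These items do not feed the primary endpoint, which is calculated from medication data.

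Finally, Statistical analyses names no covariates, so adjustment for baseline medication status, MMSE or interview items is possible but not stated. This limits the concern to adjusted analyses.

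**Conclusion.** The concern holds for baseline values and for analyses that use them. It is stated in the text that t0 follows randomisation, that data collectors are unblinded and that the first workshop is held around t0. The last of these is not consistent with the intervention starting after t0. The exposure is avoidable, because recruitment is already complete at randomisation.

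The size is unknown. It depends on how far allocation shifts t0 values and on which of them enter the model, and the article gives neither. It would be wrong to conclude that the primary result is biased as planned: a six-month comparison without baseline adjustment is unaffected, and record-based medication status is less exposed than the MMSE and interview items. The point deserves correction but does not threaten the trial as a whole.

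**What to change.** **Homes not yet randomised:** complete and lock t0 data, including the GP diagnoses and laboratory values, before the home's allocation is released. Hold the first workshop only after that lock.

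**Homes already randomised:** take any baseline medication covariate from dated home records as of a day before randomisation. Do not adjust for interview or MMSE values collected after allocation in the primary model.

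**Text:** reconcile Intervention, Randomisation, Blinding and Data collection methods on the order of randomisation, t0 and the first workshop, and on what interviewers know at t0.

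**Cost:** no extra residents. Allocation and provider training start slightly later in the remaining homes. The gain is partial: Trial status reports baseline, workshops and reviews concluded in more than half of the homes by January 2019. The lock cannot help those homes, and their post-allocation MMSE and interview baselines cannot be repaired.

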### Data management

Data will be entered in the local centres via an internet based electronic data capture (EDC) system which complies with FDA requirements (21 CFR Part 11) and the guidelines for Good Clinical Practice (GCP). The data will be stored in a central database (Oracle); there is no local data storage. The data are transferred via 128 bit SSL encryption. The access to the database and webserver is controlled by two consecutive firewall systems. Data will be stored with a pseudonym. The members of the study group have access to the electronic data entry system according a detailed concept of roles and rights. An audit trail ensures an automatic protocol of all data entries, changes and deletions.

### Statistical analyses

Because of the cluster randomisation multilevel models with the nursing home as random effect (e.g. mixed model logistic regression) will be applied for the statistical analyses of primary and secondary endpoints. Possible imbalances and confounding variables will be included in the statistical models for adjustment. The data will be analysed according the intention-to-treat principle.

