### Sample size

The sample size estimation is based on the assumption that a proportion of 50% of NHR receive PIM and/or ≥ 2 antipsychotics in Germany. This estimated figure is based on studies according to which 40% of NHR receive at least one PIM [10] and 20% receive two and more antipsychotics simultaneously [28]. We assume that an overlap of PIM and ≥ 2 antipsychotic use exists in 10%. We expect a meaningful reduction in the proportion of NHR from 50 to 30% receiving PIM and/or ≥ 2 antipsychotics.

An intracluster correlation (ICC) of ρ = 0.1 is assumed and a mean number of 25 residents per nursing home is targeted. Under these assumptions and with an α = 0.05 and a power of 80% a total of 632 residents are necessary to detect the expected difference (two-sided χ^2^-test). The one-year mortality rate is conservatively estimated as 30% [29]. With a six-months-follow-up we assume a drop-out-rate of 20% (NHR’ life expectancy in months: 47 for women/26 for men) [30]. Altogether 760 patients (and 32 nursing homes) are needed.

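### Observed imbalance is a stated ground for adjusting the primary model; a prognostic covariate set fixed in advance should replace it

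*Protocol article*

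**What the plan says.** The Statistical analyses section states that "multilevel models with the nursing home as random effect (e.g. mixed model logistic regression) will be applied" to the primary and secondary endpoints. The next sentence gives the covariate rule: "Possible imbalances and confounding variables will be included in the statistical models for adjustment". The section closes with "The data will be analysed according the intention-to-treat principle". It names no covariate, no criterion for calling a variable imbalanced, and no time by which the choice is settled.

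Four other places bear on the point:

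- **Randomisation:** "The randomisation is stratified by centres to ensure a balance in the number of nursing homes and patients" in each arm within the centres. Centre is therefore a design factor.
- **Recruitment strategy:** study nurses enter each resident's prescriptions into the trial database at baseline. The Outcomes section derives the primary endpoint from current medication data, so its baseline value can be computed.
- **Data collection methods:** baseline is taken at "t0 after obtaining written informed consent and randomization and before starting the intervention".
- **Blinding:** "blinding of participants, health care providers and data collectors is not possible". Nothing is said about the analyst.

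**The concern.** The sentence is a selection rule, not a gap that a SAP would ordinarily fill. A difference between arms becomes known only when baseline data are tabulated by arm. A model built on such differences is therefore settled after the data have been seen. In a randomised comparison the sound reason to adjust is that a variable predicts the outcome or was used in the design. A chance difference in a variable unrelated to outcome needs no correction, and a strong predictor is worth including even when the arms happen to agree on it.

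Two things are at stake. One is precision, if strong predictors enter only when they happen to differ between arms. The other is the credibility of the primary estimate. With no set, threshold or date fixed, several primary models are compatible with the text, and a reader of the results could not tell whether the reported one was chosen for its answer.

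**Working it through.** **The plan's own figure.** Inputs from the Sample size section are 50% against 30%, two-sided α 0.05, power 80%, ICC 0.1 and 25 residents per home. A 1:1 ratio is assumed, as none is stated.

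- Per arm: n = [1.96·√(2·0.4·0.6) + 0.842·√(0.5·0.5 + 0.3·0.7)]² / 0.2² = 93.
- Design effect: 1 + (25 − 1)·0.1 = 3.4.
- Total: 2·93·3.4 = 632.4, which agrees with the stated 632.

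The calculation contains no covariate, so the point leaves the sample size unchanged.

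**What the rule does to type I error.** The article gives no figure for this, so a null simulation was used. Its assumptions are illustrative: 32 homes (from Sample size), 16 per arm, a linear model on home-level values, 3 or 5 baseline covariates jointly explaining 20% or 50% of between-home variance, and 3,000 runs per setting. A covariate counted as imbalanced at p < 0.10. Rejection rates at nominal 5% were:

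| Analysis | 3 cov., 20% | 3 cov., 50% | 5 cov., 20% | 5 cov., 50% |
|---|---|---|---|---|
| Unadjusted | 3.7% | 4.7% | 4.4% | 5.5% |
| All covariates, pre-specified | 5.2% | 4.8% | 5.1% | 5.5% |
| Only imbalanced covariates, mechanical rule | 3.4% | 3.1% | 4.0% | 3.6% |
| Most favourable of the three models above | 6.8% | 8.3% | 7.8% | 9.8% |
| Most favourable covariate subset | 8.9% | 13.7% | 13.1% | 19.9% |

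The Monte Carlo standard error near 5% is √(0.05·0.95/3000) = 0.4 percentage points. The lower unadjusted values are partly noise, and only the pattern should be read: the mechanical rule sits below the nominal level, and free choice sits above it.

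**What the rule does to precision.** In the same set-up, let K be the number of covariates and R² the share of between-home variance that they explain. Adjusting for all K multiplies the variance of the arm difference by about (1 − R²)·(32 − 3)/(32 − 3 − K).

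- K = 3, R² = 0.5: 0.5·29/26 = 0.56, so the standard error falls to √0.56 = 0.75 of its unadjusted value.
- K = 5, R² = 0.2: 0.8·29/24 = 0.97, so the standard error falls only to √0.97 = 0.98.

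A short list of strong predictors therefore gains precision, while a longer list of weak home-level ones gains almost nothing. Under a p < 0.10 rule, by construction, each covariate enters in about one randomisation in ten. A strong predictor would be left out in the other nine, and most of the gain would be lost.

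**The case against.** Much can be said for the article. It is a short summary, and a list of covariates commonly sits in the SAP, so the absence of named variables is not itself a fault. The rule mentions confounding variables as well as imbalances. A confounder must be related to outcome, so prognostic value is not excluded. Imbalance can be assessed on t0 data before any t1 outcome exists, which is not the same as choosing a model by its result. Non-chance differences are also conceivable: Table 1 excludes pharmacists and GPs who serve homes in both arms, and the Challenges section anticipates that professionals will discontinue.

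These arguments limit the harm but leave the criterion standing. The article did not stay silent; it made imbalance a ground for inclusion. If a SAP list exists, this sentence should agree with it. If non-chance differences are feared, the variables at issue can be named beforehand.

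Three stronger readings are tempting, and the documents do not support them:

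- **That adjusting for imbalance inflates type I error in itself.** The mechanical rule was mildly conservative; inflation appeared only with discretionary choice.
- **That the analysts know the allocation.** The Blinding section covers participants, providers and data collectors, and is silent on analysts.
- **That the harm can be measured by how often some baseline variable would look imbalanced.** That count depends on the number of variables, their ICCs and a testing method that the article does not give, and it is not an error rate for the treatment comparison.

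Nor do resident-level covariates use up the information from 32 homes to any great extent; that cost belongs mainly to home-level covariates.

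**Conclusion.** The point holds as a defect in the stated criterion. The covariate set depends on between-arm comparisons of baseline data, while centre and the baseline value of the primary endpoint go unmentioned. A fixed mechanical version would cost precision rather than validity. The open version in the text leaves room for choice in an open-label trial with no stated analyst blinding. Under the assumptions above, such choice could raise a nominal 5% error to 6.8–19.9%, depending on how freely models are selected.

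Those figures come from a linear home-level model with assumed covariates, not from the planned mixed logistic model. They show direction and rough size, and do not predict what this trial will do. The article nowhere says that a favourable model will be picked. The point does not invalidate the trial, but the sentence should be changed.

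**What to change.** Replace the sentence on imbalances and confounders with a covariate set for the primary model, fixed and dated before t1 data are examined:

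- centre, as the stratification factor;
- baseline status on the primary endpoint (PIM and/or ≥ 2 antipsychotics), defined exactly as at t1;
- at most a few further variables, each named and chosen because it is expected to predict the outcome.

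State that no covariate enters the primary model because of an observed difference between arms, and that any model adding one is a labelled sensitivity analysis. Apply the same principle to the secondary endpoints, with each endpoint's own baseline value where it is collected. If the SAP already lists covariates, make the two texts agree.

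The cost is a few lines of text. Baseline medication is already recorded, so no new data are needed, and the sample size stays as calculated.
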